#### **b) Analysis of ORR**

The difference in ORR between the two arms will be assessed with the Chi-square test. The 95% CIs for ORR will be generated through the Clopper-Pearson method.

#### **c) Analysis of DoR**

The difference in DoR between the two arms will be evaluated with the Log-rank test. The HR and its 95% CI will be calculated using the Cox proportional hazards model.

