## 5. Study Endpoints

The endpoints of this study will be analyzed based on the tumor response assessment by investigator per Response Evaluation Criteria in Solid Tumors (version 1.1) (RECIST 1.1).

Primary endpoint is 18-month PFS rate.

Secondary endpoints consist of PFS, confirmed objective response rate (ORR, the proportion of patients with confirmed complete response or partial response), duration of response (DoR, time from the first documented response to the first time of disease progression or death), safety, and OS.

Exploratory endpoints consist of PFS benefits in patients with central nervous system (CNS) metastasis, *EGFR* ex19del, *EGFR* L858R mutation, and other mutational events.

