### **9.1.5 Duration of Response (DoR)**

DoR is defined as the time from the date of first compliance with response to the date of PD or death due to any cause. The end date of the response should be

consistent with the date of the endpoint PFS. The start of DoR is defined as the latest date of the visit at which PR or CR criteria are first met. If a subject does not progress after a response, the censored time for PFS will be used for DoR.

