## **10.1 Efficacy Analysis**

Efficacy endpoints will be analyzed in Full analysis set (FAS) using results evaluated by the investigator as per RECIST 1.1.

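### Duration of response is compared between arms by log-rank test and Cox model although only responders have one, so the p-value and hazard ratio are not a randomised comparison (minor)

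*Protocol*

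**What the plan says.** DoR is a secondary endpoint (protocol section 5). Section 9.1.5 sets its clock: "DoR is defined as the time from the date of first compliance with response to the date of PD or death" from any cause. The only censoring rule for it also presupposes a response: "If a subject does not progress after a response, the censored time for PFS will be used for DoR".

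Section 10.1.2 c) then fixes the analysis: "The difference in DoR between the two arms will be evaluated with the Log-rank test", followed by "The HR and its 95% CI will be calculated using the Cox proportional hazards model". The PFS analysis in 10.1.2 a) has the same structure. For the response rate (ORR), 10.1.2 b) says: "The difference in ORR between the two arms will be assessed with the Chi-square test".

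Section 10.1 assigns the efficacy endpoints to the full analysis set (FAS). The protocol nowhere gives a non-responder a DoR value, nowhere calls the DoR comparison descriptive, and offers no version of it over all randomised patients.

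**The concern.** PFS exists for every randomised patient and runs from randomisation, so a log-rank test on it compares the groups that randomisation created. DoR exists only for patients who respond, and response is an outcome that the treatment can change. The plan itself tests whether ORR differs between the arms. Comparing DoR by arm conditions on that outcome.

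Suppose the combination turns some non-responders into patients with short responses. Its responder group then contains patients whose counterparts in the control arm are left out. DoR looks worse on the combination although those patients gained a response and nobody lost anything. Other patterns of selection could favour the combination. At stake is a secondary-endpoint p-value and HR that a reader would take for a treatment effect.

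**Working it through.** **Step 1: who enters the comparison.**
- PFS (9.1.2) starts at randomisation and is defined for all patients.
- DoR (5 and 9.1.5) starts at first response and is undefined without one. The censoring rule does not change this.
- The FAS label (10.1) does not bring non-responders in, because no rule gives them a value.
- The set compared in 10.1.2 c) is therefore the responders. The words responders only do not stand in that section; they follow from the definition.

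**Step 2: the plan's own figure.** The protocol states no event number, power or alpha for DoR, so there is none to reproduce. N = 98 rests on 18-month PFS rates of 75% and 50% (section 6) and does not involve DoR.

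**Step 3: illustration of the medians.** All inputs are assumed, because the protocol gives no first-line ORR or DoR.
- Control: 34 responders of 49 (34/49 = 69%), exponential DoR with median 18 months.
- Combination: the same 34, plus k = 5 or 8 added responders with median m = 6 or 8 months. ORR is then 39/49 = 80% or 42/49 = 86%.
- Treatment changes no duration among the 34.

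The combination median x solves

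(34·2^(−x/18) + k·2^(−x/m)) / (34 + k) = 0.5.

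Check at k = 8, m = 6 with x = 14.45: 34·2^(−14.45/18) = 19.49 and 8·2^(−14.45/6) = 1.51. The sum is 21.0, half of 42.

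**Step 4: effect on the test that the plan fixes.** The same scenarios were simulated with censoring at 24 months (assumed), 5,000 trials each, two-sided 0.05.

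| k | m (months) | Combination median (months) | Apparent loss against 18 | Log-rank rejects |
|---|---|---|---|---|
| 5 | 8 | 16.1 | 1.9 | 5.7% |
| 5 | 6 | 15.6 | 2.4 | 6.7% |
| 8 | 8 | 15.3 | 2.7 | 6.8% |
| 8 | 6 | 14.4 | 3.6 | 9.4% |

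The HR runs from about 1.10 to 1.21 across these rows; a separate run gave 1.11 to 1.22. Two Monte Carlo standard errors are at most 2·√(0.094·0.906/5000) = 0.8 percentage points, so the rejection rates are best read as about 6 to 9%.

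**Step 5: what the distortion needs.** A second simulation drew responders at random from 49 patients per arm (24-month censoring, 4,000 trials, no effect on duration in any patient type). Patients who respond on either treatment have median DoR 18 months.

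| ORR control vs combination | Median DoR of added responders | Rejection | HR |
|---|---|---|---|
| 70% vs 70% | none added | about 5% | about 1.00 |
| 60–70% vs 80% | 18 months | 4–5% | about 1 |
| 70% vs 80% | 6–9 months | 6–7% | 1.09–1.13 |
| 65% vs 80% | 6–9 months | 7–9% | 1.14–1.21 |
| 60% vs 80% | 6–9 months | 8–13% | 1.18–1.29 |

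With equal ORR there is no distortion in this model, and there is none when the added responders have the same prognosis. It takes both a difference in ORR and a difference in prognosis.

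**The case against.** The strongest reply is that little depends on this result. The trial is phase II, its primary test is on the 18-month PFS rate, and DoR is one of several secondary endpoints with no alpha, hierarchy or success claim attached. Comparisons over the FAS are already planned for PFS and ORR, so a reader can see whether the response rates differ and what happens in all patients. This stands and sets the severity. It does not turn the DoR HR into a randomised comparison.

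A second reply is that the distortion is modest and rests wholly on assumed inputs. This also stands: rejection of about 6 to 9% is not far above 5%, and only one direction has been illustrated.

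A third reply is that Kaplan-Meier medians by arm carry the same selection as the test, so dropping the p-value alone would leave the apparent loss of 2 to 3.6 months in view. This is correct, and it is why the medians need a label and why any comparison has to move to all randomised patients.

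Deferral to an analysis plan is only a partial answer, since the protocol itself names the test and the effect measure.

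A reader might infer that the DoR result will be biased against the combination, or that the trial's error rate is inflated. The documents support neither: they give no ORR or DoR from which a direction could be derived, and the primary test does not use DoR.

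**Conclusion.** The point holds as a minor one. Section 10.1.2 c) fixes a between-arm test and HR on a group formed by a post-randomisation outcome, and nothing elsewhere in the protocol repairs or qualifies this. That conclusion rests on the definitions alone.

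The size does not. The figures above depend on assumed response rates, exponential durations, short responses among the added responders and 24-month censoring. They show that a misleading result is possible without harm to any patient; they do not predict one. Nor does the point make responder-only DoR unfit to report: as a description of how long responses last in each arm it remains useful.

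**What to change.** In 10.1.2 c), remove the log-rank p-value and the HR for responder-only DoR. Report Kaplan-Meier medians with 95% CIs by arm, labelled as descriptive and conditional on response. If a between-arm comparison is wanted, base it on time in response over all randomised patients in the FAS, with non-responders counted as zero, and name the measure and its time horizon in advance.

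The opening paragraph of section 10 assigns the log-rank test to time-to-event variables in general, so it should except DoR to stay consistent.

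The cost is the rewording of two sentences, a short exception in section 10, and the loss of one nominal secondary p-value with its HR. Visits, data collection, the primary analysis and the sample size do not change.

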### **10.1.3 Analysis of Exploratory Endpoints**

The PFS benefits in patients with CNS metastasis, *EGFR* exon 19 deletion, *EGFR* L858R mutation, and other mutational events will be estimated using the Log-rank test. The HR and its 95% CI will be calculated using the Cox proportional hazards model.

### **10.1.4 Time of Interim Analysis**

The interim analysis will be initiated after all patients undergoing treatment have been followed up for over 18 months.

### **10.1.5 Time of Final Analysis**

The final analysis for OS will be conducted after 59 death events (data maturity, 60%).

## **10.2 Safety Analysis**

### **10.2.1 Adverse Events**

The AEs that occur from the initiation of treatment until 30 days after the last dose will be summarized in the safety evaluation. The AEs that occur prior to initiation of treatment and AEs that occur after 30 days following the last dose will be tabulated separately and not included in the summary table of AEs.

Treatment-emergent AEs will be summarized by treatment group, mainly including:

- 1) Number and proportion of subjects with at least one AE;
- 2) Number and proportion of subjects with at least one treatment-related AE;
- 3) Number and proportion of subjects with at least one severe (CTCAE Grade  $\geq 3$ ) AE;
- 4) Number and proportion of subjects with at least one severe (CTCAE Grade  $\geq 3$ ) treatment-related AE;
- 5) Number and proportion of subjects with at least one SAE;
- 6) Number and proportion of subjects with AEs resulting in dose modification;
- 7) Number and proportion of subjects with AEs resulting in withdrawal;
- 8) Number and proportion of subjects with AEs resulting in death.

All AEs will be summarized by system organ classes and preferred term. All AEs will be tabulated.

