#### **Calculation of Sample Size:**

Given assumptions of 18-month PFS rate of 75% for aumolertinib plus apatinib and 50% for aumolertinib alone, a drop-out rate of 10%, at the significance level of 0.05, to achieve the power of 0.8, a total number of 98 subjects are needed (49 per arm).

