## 6. Sample Size

This is a multicenter, randomized, open-label study with a superiority design. The primary endpoint is 18-month PFS rate. Based on the assumptions of 18-month PFS rate of 75% for aumolertinib plus apatinib and 50% for aumolertinib alone, a drop-out rate of 10%, at the significance level of 0.05, to achieve the power of 0.8, a

total number of 98 subjects are needed (49 per arm).

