#### **1) Aumolertinib + apatinib group:**

Aumolertinib: strength: 55 mg/tablet; dose: 110 mg/day (2 tablets/day), p.o. QD;

Apatinib: strength: 250 mg/tablet; dose: 250 mg/day (1 tablet/day), p.o. QD.

2) Aumolertinib monotherapy group:

Aumolertinib: strength: 55 mg/tablet; dose: 110 mg/day (2 tablets/day), p.o. QD;

Each treatment cycle consists of 21 days of continuous administration. After treatment is started, efficacy will be evaluated once every 6 weeks ( $\pm 7$  days) as per RECIST 1.1. Subjects will continue treatment until progressive disease assessed by investigator per RECIST 1.1 or until the withdrawal or discontinuation criteria are met. Subjects may continue to receive the treatment even if progressive disease per RECIST 1.1 occurs as long as they still benefit from the treatment as judged by investigator; if it is decided to continue the treatment, the baseline and follow-up plan will not be affected by the additional courses of treatment. Once the treatment is discontinued due to lack of clinical benefit upon judgment, it cannot be started again.

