## **9.2 Safety Evaluation**

All safety data will be summarized at the end of the study. All data from the initiation of treatment until 30 days after the last dose will be summarized together in the safety evaluation. Data prior to initiation of treatment will be summarized but not included in the summary table of AEs.

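### Adverse events are summarised only as crude proportions over an on-treatment window whose length depends on progression, so between-arm differences mix toxicity with exposure for events that accrue over time

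*Protocol*

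**What the plan says.** Section 8.2 ties treatment to progression: "Subjects will continue treatment until progressive disease assessed by investigator per RECIST 1.1 or until the withdrawal or discontinuation criteria are met". It also allows treatment to continue beyond progression if the investigator judges that the patient still benefits.

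Section 10.2.1 sets the AE window: "The AEs that occur from the initiation of treatment until 30 days after the last dose will be summarized in the safety evaluation". It then lists eight summaries by treatment group, each a number and proportion of subjects. The list is introduced as the main content, so it is not closed. Section 9.2 gives the timing: "All safety data will be summarized at the end of the study".

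Section 7.1 gives the purpose of the trial as comparing the efficacy and safety of the two regimens. Section 10 assigns the Chi-square test to between-group differences in categorical variables, without naming AEs. Section 6 designs the trial on an "18-month PFS rate of 75% for aumolertinib plus apatinib and 50% for aumolertinib alone".

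The protocol mentions no summary of treatment duration, no exposure-adjusted rate and no time-to-first-event summary of AEs.

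**The concern.** A patient contributes AEs only while on drug and for 30 days afterwards. If one arm delays progression, its patients stay longer in that window and have more time to record a first event. The proportion with at least one event can then be higher in that arm even when the monthly risk is the same.

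Safety is a named secondary endpoint and part of the stated objective. The crude table is also the only safety contrast that the protocol describes. If the combination works as planned, part of any excess of late or cumulative events could reflect its efficacy. Without exposure data beside the table, a reader cannot tell how much, or in which direction.

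**Working it through.** **The plan's own figure.** The protocol gives no figure for exposure or AE incidence. The relevant design inputs are the PFS rates behind the sample size. That figure reproduces with one-sided alpha 0.05 and unpooled variance: (1.645 + 0.842)² × (0.75×0.25 + 0.5×0.5) / 0.25² = 43.3, so 44 per arm; 44/0.9 = 48.9, so 49 per arm and 98 in total. This shows only that 75% and 50% are the rates the design uses.

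**Assumptions (not in the protocol).** PFS is exponential through the stated rates. Treatment stops at progression. The first-event hazard h is constant and identical in both arms. Data cuts are at month 18 and, for illustration, month 36. A hazard of 0.02 per month is a one-year risk of 1 − exp(−0.24) = 21%; 0.05 is 1 − exp(−0.60) = 45%.

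**Progression hazards.**
- Control: ln 2 / 18 = 0.0385 per month.
- Combination: −ln(0.75) / 18 = 0.0160 per month.

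**Mean time on treatment to cut T**, (1 − exp(−λT)) / λ:

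| Cut | Combination | Control | Ratio |
|---|---|---|---|
| Month 18 | 15.6 months | 13.0 months | 1.20 |
| Month 36 | 27.4 months | 19.5 months | 1.41 |

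**Crude proportion with a first event**, h/(h + λ) × (1 − exp(−(h + λ)T)):

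| h per month | Cut | Combination | Control | Difference |
|---|---|---|---|---|
| 0.02 | 18 | 26.5% | 22.3% | 4.2 points |
| 0.05 | 18 | 52.7% | 45.0% | 7.7 points |
| 0.02 | 36 | 40.4% | 30.0% | 10.3 points |
| 0.05 | 36 | 68.7% | 54.2% | 14.6 points |

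**With the 30-day tail.** Extending each window by one month after stopping, capped at the cut, gives 27% versus 23% and 53% versus 47% at month 18. At month 36 it gives 41% versus 31% and 70% versus 56%. The gap narrows slightly, to about 4 to 7 points and 10 to 14 points.

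**Early events only.** With h = 0.10 per month confined to the first 3 months, the same formula at T = 3 gives 25.3% versus 24.5%, a difference of 0.8 points.

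**What cancels it.** An extra discontinuation hazard in the combination arm of 0.0385 − 0.0160 = 0.0225 per month, or 1 − exp(−0.0225×12) = 24% stopping by month 12, equalises exposure and removes the artefact. A larger hazard reverses it.

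**Scale.** With 49 per arm and proportions near 30%, the standard error of a difference is √(2 × 0.3 × 0.7 / 49) = 9.3 points. The month-18 artefact is below that; the month-36 artefact is about the same size or larger.

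**The case against.** The strongest case against is that nothing here is misstated. Crude proportions over a treatment-emergent window are a standard description, and they answer a real question: what patients experience over their whole course of treatment. Section 10.2.1 says that AEs are summarised by arm and names no AE test. Its list is open, and exposure tables are often left to a statistical analysis plan, which is not shown. All of this stands, and it lowers the weight of the point. It does not remove it, because the protocol does name the measure and the window, and every measure it names is affected. Section 7.1 makes comparison of safety a purpose of the trial, so the table will be read that way.

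Two stronger readings are tempting, and the documents do not support them.

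- A reader might infer that the design assumes much longer treatment with the combination. The protocol assumes PFS rates, not treatment durations. Treatment may continue past progression in either arm and may stop earlier under the discontinuation criteria. Modelled mean exposure is only 1.20 times longer at month 18. The ratio of 1.41 needs extrapolation to month 36, a cut the protocol does not name. Study end and the 59-death final analysis carry no dates.
- A reader might infer that identical toxicity must look worse in the combination arm. That holds only for events that accrue over time, and only if toxicity does not shorten treatment there. The protocol gives no discontinuation rate, so the direction cannot be settled from it.

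**Conclusion.** The point holds as a caution about interpretation. The safety summaries that the protocol names are crude proportions over a window tied to an outcome the design expects to differ between arms. With identical constant hazards of 0.02 to 0.05 per month, exponential PFS through 75% and 50%, and treatment until progression, the combination arm would show about 4 to 8 points more at month 18 and 10 to 15 points more at an assumed month-36 cut. The artefact is under 1 point for events confined to the first 3 months. Toxicity-driven stopping in the combination arm could cancel or reverse it.

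The primary efficacy analysis is untouched, and the crude table is not an error. This is a low-priority improvement that costs little.

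**What to change.** Keep the crude table in Section 10.2.1 and add:

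1. Duration of exposure to each drug, by arm.
2. For grade 3 or higher AEs, SAEs and treatment-related AEs, cumulative incidence of the first event within a fixed common window, for example the first 12 months. State how patients whose AE window ends earlier are handled. A plain count within 12 months would not be enough: in the model above it still gives 19.5% versus 17.2% for h = 0.02 and 41.5% versus 37.0% for h = 0.05. A time-to-first-event estimate that censors at the end of the AE window gives the same value in both arms, 21% and 45%, provided that stopping is unrelated to AE risk.
3. Exposure-adjusted first-event rates (first events per patient-month at risk) as a supplement.

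Add one sentence saying that between-arm safety differences will be interpreted with these beside the crude figures. Replacing crude proportions as the lead measure should not be required, since each measure involves a trade-off.

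The cost is a few extra tables from first-dose, last-dose and AE-onset dates. The synopsis already requires AE onset and duration to be recorded. The downside is that exposure-adjusted rates assume a roughly constant hazard, which the fixed-window estimate does not need.

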#### **Safety Evaluation:**

Observe and record any adverse events experienced by subjects during the clinical trial period, including clinical symptoms, abnormal vital signs, and abnormal laboratory tests; record severity, time of onset, duration, treatment method, and prognosis; and determine its relatedness to the study drug. Safety endpoints: Occurrence of adverse events; occurrence of serious adverse events; proportion of dose modification, patients withdrawn or due to adverse events.

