### **8.3 Follow-up Period**

Subjects who discontinue the treatment due to meeting the discontinuation criteria should complete the treatment discontinuation follow-up, the 30 days safety follow-up after treatment discontinuation, and survival follow-up once every 12 weeks ( $\pm 7$  days) as specified in the study plan.

Subjects without progressive disease at treatment discontinuation will be followed up once every 6 weeks ( $\pm 7$  days) until progressive disease assessed by investigator per RECIST 1.1 (both intracranial and systemic), even if the subject has received other anti-tumor treatments; after progressive disease, the subjects will be followed up for survival once every 12 weeks as specified in the study plan.

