#### **9.1.4 Confirmed Objective Response Rate (ORR)**

As per RECIST 1.1, confirmed ORR is defined as the percentage of subjects with complete response (CR) or partial response (PR) lasting for at least 2 times evaluation before PD.

Data until PD or last evaluable data in the absence of PD will be recorded in the assessment of ORR. However, any CR or PR that occurs after discontinuation of the study treatment and further anti-tumor treatment will not be included in the calculation of ORR.

Table 2 provides the criteria used to determine objective tumor response of TLs.

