## Appendix A Study Plan

| ● Randomized treatment study plan        |                  |                  |          |                        |               |                  |                                          |                                        |
|------------------------------------------|------------------|------------------|----------|------------------------|---------------|------------------|------------------------------------------|----------------------------------------|
| Visit                                    | Screening period | Treatment period |          |                        | EOT follow-up | Follow-up period |                                          |                                        |
|                                          | 1                | 2                | 3-7      | 8+                     |               | 28-day follow-up | Progression follow-up once every 6 weeks | Survival follow-up once every 3 months |
| Treatment cycle/Day                      |                  | C1 D1            | C2-C6 D1 | C7 +, every 6 weeks D1 | NA            | NA               | NA                                       | NA                                     |
| Day                                      | -28              | 1                | 22-126   | 127+                   | NA            | NA               | NA                                       | NA                                     |
| Time window (days)                       | NA               | 0                | ± 7      | ± 7                    | ± 7           | ± 7              | ± 7                                      | ± 7                                    |
| Informed consent                         | ×                |                  |          |                        |               |                  |                                          |                                        |
| Demographic and baseline characteristics | ×                |                  |          |                        |               |                  |                                          |                                        |
| Medical/Surgical history                 | ×                |                  |          |                        |               |                  |                                          |                                        |

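### The main adverse event summary runs to 30 days after the last dose with no cut-off at the start of new anti-tumour therapy, and Appendix A closes follow-up at a different day

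*Protocol*

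**What the plan says.** Section 10.2.1 of the protocol sets the reporting window: "The AEs that occur from the initiation of treatment until 30 days after the last dose will be summarized in the safety evaluation". Section 9.2 repeats it: "All data from the initiation of treatment until 30 days after the last dose will be summarized together in the safety evaluation". Section 10.2.1 holds out only events before treatment and those after the window: "AEs that occur after 30 days following the last dose will be tabulated separately and not included in the summary table of AEs". It then lists eight rows of treatment-emergent events by arm, without defining treatment-emergent in any other way.

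For response, the protocol does separate the effect of later therapy. Section 9.1.4 states that "any CR or PR that occurs after discontinuation of the study treatment and further anti-tumor treatment will not be included" in the ORR.

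On the visit that closes the window, section 8.3 requires "the 30 days safety follow-up after treatment discontinuation". The corresponding column in Appendix A is headed "28-day follow-up" and carries a window of ±7 days. Within that same column, the concomitant medication cell refers to 30 days.

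**The concern.** A patient who progresses, stops study drug and starts another treatment within days is still inside the 30-day tail. An adverse event caused by the new treatment is then counted as treatment-emergent for the randomised arm. Section 8.3 foresees such treatment, since it continues progression follow-up in patients who have already received it.

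Safety is a secondary endpoint, and the added toxicity of apatinib has to be weighed against any gain in PFS. The all-cause rows are where that comparison is read, and with 49 patients per arm one patient moves a rate by 1/49 = 2.0 percentage points.

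The differing visit day raises a second question: whether any scheduled contact covers the end of the window over which events are to be counted.

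**Working it through.** **What the rule counts.** The protocol gives no figure on this point to reproduce, so the first step is to go through the rows of section 10.2.1.

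- Any AE, grade 3 or higher AE, SAE and fatal AE are all-cause rows. An event that starts after new therapy, but by day 30, enters them.
- The two treatment-related rows are partly protected, because relatedness is assessed.
- The dose modification and withdrawal rows should be almost untouched, because study drug has already stopped.

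Four of the eight rows are therefore exposed.

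**Direction.** Section 6 plans 18-month PFS rates of 50% for control and 75% for the combination, with 49 patients per arm. Treating PFS events as progressions:

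- control: 49 × (1 − 0.50) = 24.5 by 18 months
- combination: 49 × (1 − 0.75) = 12.25 by 18 months

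Section 9.2 summarises safety at the end of the study, so later times matter too. If PFS is exponential through the planned rates (an assumption), the proportions progressed are:

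- 36 months: 1 − 0.50² = 75% and 1 − 0.75² = 44%
- 48 months: 1 − 0.50^(48/18) = 84% and 1 − 0.75^(48/18) = 54%

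The ratio falls from 2.0 to about 1.6, but the gap in points stays at 25 to 31.

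Stopping for toxicity works the other way. If one third of the progression-free combination patients stopped for adverse events and moved to other therapy by 18 months, with none doing so in control, the combination total would be 0.25 + 0.75 × 1/3 = 0.50, equal to control. The documents give no rate for this.

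**Size, for illustration only.** Assume that:

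- all progressors stop at progression;
- a share f = 30% to 70% start new therapy inside the 30-day tail;
- a share q = 5% to 30% of those have a countable event in a given row only because of that therapy.

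None of these values is in the protocol. Added rate = proportion progressed × f × q, at 18 months:

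| | Low (f = 0.30, q = 0.05) | High (f = 0.70, q = 0.30) |
|---|---|---|
| Control, 0.50 × f × q | 0.75 points (0.4 of 49) | 10.5 points (5.1 of 49) |
| Combination, 0.25 × f × q | 0.375 points (0.2 of 49) | 5.25 points (2.6 of 49) |
| Difference | 0.375 points (0.2 of 49) | 5.25 points (2.6 of 49) |

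At 36 months the high end would be (0.75 − 0.4375) × 0.70 × 0.30 = 6.6 points, or 3.2 of 49. The difference is thus about 0 to 3 patients, before any offset from stopping for toxicity.

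**The closing visit.** A visit at 28 ± 7 days falls between day 21 and day 35. The window ends at day 30, so the visit may come up to 30 − 21 = 9 days before it closes.

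**The case against.** A fixed 30-day tail is a legitimate convention, sections 9.2 and 10.2.1 agree with each other, and an SAP that is not shown could narrow the definition of treatment-emergent. The ORR rule serves another purpose and creates no contradiction. Much of this is fair. However, section 10.2.1 states both what enters the summary and what is held out, so a cut at new therapy would depart from the protocol text and not merely fill a gap in it.

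A reader might infer that control is inflated more, so that the combination's extra toxicity is hidden. The documents do not establish this. Progression is not the same as stopping and switching: section 8.2 allows treatment beyond progression. Section 9.3 recommends discontinuation when the lowest apatinib dose is not tolerated, a route out of treatment specific to the combination arm. The planned PFS rates support a likely direction and no more.

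The effect is also small against sampling error. If the rates were 30% and 50% (an assumption), the standard error of the difference would be √(0.30 × 0.70/49 + 0.50 × 0.50/49) = 9.7 points. The protocol also has a safeguard: investigators must "determine its relatedness to the study drug", and one row reports "Number and proportion of subjects with at least one treatment-related AE", with a matching row for grade 3 or higher. That mitigation stands, but it does not extend to SAEs or deaths, and relatedness is judged open-label.

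A reader might also infer from the 9 days that adverse event data will be lost. That is not shown. Later visits can record such events, and the span of the adverse event row in Appendix A cannot be read in the available text.

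Finally, a cut at new therapy shortens the observed tail unequally between arms. This is a fair criticism, and the fix has to allow for it.

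**Conclusion.** The point holds as a modest defect. As written, sections 9.2 and 10.2.1 put next-line toxicity arising within 30 days of the last dose into the any-AE, grade 3 or higher, SAE and fatal rows of the randomised arm. This follows from the text and needs no assumption.

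That the arms may be affected unequally is reasonable. That control is affected more is only an inference from the planned 50% and 75%, and it could be cancelled by toxicity-driven stopping in the combination arm. The size cannot be derived from the documents; the figure of about 0 to 3 patients between arms rests wholly on the assumed f and q and on all progressors stopping at progression.

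The conflict between the 28-day column in Appendix A and the 30 days in sections 8.3, 9.2 and 10.2.1, and in the appendix's own concomitant medication cell, is plain on the text. These passages must be reconciled.

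**What to change.** 1. In sections 9.2 and 10.2.1, end the main adverse event summary at the earlier of 30 days after the last dose and the day before the first subsequent anti-tumour treatment.
2. Put events from that start up to day 30 in the separate tabulation that section 10.2.1 already plans, and show there which are judged related to study drug, so that delayed toxicity stays visible.
3. Report the full 30-day summary as a sensitivity check, because the cut shortens the tail unequally.
4. Ensure that the start date of new therapy is recorded. Appendix A marks the anti-tumour treatment row only at screening, progression follow-up and survival follow-up, and not at the 28-day visit.
5. Reconcile the 28-day column of Appendix A with the 30-day text, so that the contact closing the adverse event window does not come before the window ends.

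The cost is a reworded sentence in each of two sections, one programming rule, one extra table, a check on one data field and a correction to the schedule. The downside is that a few unrelated late events move from the main table to the separate one.
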